**Table 1 Tab1:** **Oral nutritional supplement composition**

ONS	Volume (ml)	Kcal/ml	Energy content (kcal) per serving	Protein content (g) per serving
Fortisip bottle (Nutricia)	200	1.5	300	12
Fortisip compact (Nutricia)	125	2.4	300	12
Nutriplen (Nualtra)	125	2.4	300	12

Nutritional information taken from http://www.nutricia.ie/products and http://nualtra.ie/information-for/dietitian.

The primary researcher continued to make dietetic visits to the care homes on a monthly basis and determined compliance with the intervention at 3 and 6 months. The care home staff were required to record intake of ONS on the daily drugs chart, as a proportion taken. The average intake will be calculated from three non-consecutive charts at 3 and 6 months. Compliance will be categorised into ‘compliant’, if 75% or more of the advised dose is consumed daily and ‘non-compliant’ if less than 75% is consumed.

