### Aims and objectives

The primary aim is to assess the feasibility of conducting a definitive trial in UK care home setting, in terms of recruitment and retention, use and acceptability of the nutritional interventions, follow-up at 3 and 6 months and the feasibility and acceptability of outcome measures and data collection methods.

The following criteria will be used to assess success:Recruitment target for care homes (six) and for residents (*n* ≥ 50) met in the time available (3 months)Favourable difference shown in the number of residents at risk of malnutrition and the number deemed eligible to participate (≤20%)Retention rate at 100% for care homes, at 6-months follow-up and at 65% or more for residents, accounting for the expected high mortality and attrition rateIntervention crossover of less than 10% for each interventionMore than 80% of residents to be compliant with 50% of the dietetic-led intervention dose (≥300–450 kcal) and more than 60% of residents to be compliant with 75% or more of the dietetic-led intervention dose (≥450–600 kcal)85%–90% staff adherence to intervention scheduleData completeness of ≥80% for each outcome measure and data collection method

Components of the trial that are deemed to be infeasible or unacceptable will be modified in the definitive trial or will be removed altogether.

The trial will also examine, qualitatively, the acceptability of the interventions, outcome measures and data collection methods to malnourished care home residents and care home staff.

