#### Food-based intervention

The content of the food-based intervention was based on the developed resources and guidelines of the Solihull Nutrition Support Project, the PrescQIPP Nutrition Toolkit [36] and the Malnutrition pathway [37], which was developed and agreed by a multi-professional consensus panel. Assigned care staff within the care homes randomised to food-based intervention received face-to-face instruction by the primary researcher to increase participating resident’s daily nutritional intake by 600 kcal and 20–25 g protein, using agreed interventions, alongside the standard care home nutritional intervention for malnutrition. Food-based interventions included the provision of homemade enriched drinks between meals and/or the provision of between-meal fortified snacks. The intervention combination agreed by the primary researcher and the care home staff was documented for each resident, at baseline and at 3 months. The intervention recipes and a breakdown of the calorie and protein content were provided to the care home staff and catering teams.

The primary researcher continued to make dietetic visits to the care homes on a monthly basis and determined compliance with the intervention at 3 and 6 months. The care home staff were required to record resident intake of the food-based intervention on the daily food record chart, as a proportion taken. The average intake will be calculated from a three non-consecutive records at 3 and 6 months. Compliance will be categorised into ‘compliant’, if 75% or more of the advised food/beverage is consumed daily and ‘non-compliant’ if less than 75% is consumed.

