### Outcome measures

#### Primary outcome measures

Feasibility considerations:

Recruitment of care homes (ratio between those who consented to participate and those who were approached)The suitability of resident eligibility criteria (ratio between those who were considered eligible to enter the trial and those who were at risk of malnutrition)Residents’ willingness to participate in PROM’s (ratio between those who consented to participate and those who were eligible and approached)Resident retention in the trial (ratio between those who entered the trial and those that remained at 3 months and at 6 months)Data collection (ratio between completed questionnaires/screening tools/record charts and non-completed or unavailable questionnaires/screening tools/record charts) and physical outcome measurements (ratio between those residents measured and those that could not be measured)

Acceptability considerations:

Resident acceptability of allocated interventions (as measured by compliance and crossover rate in each intervention arm)Staff acceptability of allocated interventions (as measured by adherence to intervention plan)Resident acceptability of physical measurements (as measured by the ratio between those residents measured and those that refused)Resident acceptability of PROM’s data collection tools: appetite and dietary satisfaction VAS tool, EQ5D VAS and questionnaire, COOP quality of life tool. Questionnaire completion rates will be calculated

Secondary outcome measures:

Changes in nutritional status (malnutrition risk score, weight, body mass index, mid arm muscle circumference), functional status (hand grip strength), nutritional intake (energy, protein, fluid), healthcare resource usage and PROM’sUsefulness of resident completed questionnaires and tools (appetite and dietary satisfaction VAS, EQ5D VAS and questionnaire, COOP tool) and staff completed questionnaires and tools (sMMSE, healthcare resource usage). The ratio between those residents in the trial with capacity and those residents in the trial, but lacking capacity will be recorded. Questionnaire completion rates will be calculated and any third-party help used in completion will be recorded

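### Compliance is classified from three charts at each of two visits although intake is charted daily, so individual classification is imprecise and early leavers are not counted

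*Protocol article*

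**What the plan says.** Compliance appears at three places in the protocol article.

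- **Success criteria (Aims and objectives).** More than 80% of residents should reach 50% of the dose, and the second limb asks for "more than 60% of residents to be compliant with 75% or more of the dietetic-led intervention dose".
- **Primary outcome measures.** Resident acceptability of the allocated interventions is measured by compliance and by crossover in each arm.
- **Measurement rule.** In the ONS arm, staff are to "record intake of ONS on the daily drugs chart, as a proportion taken", and then "The average intake will be calculated from three non-consecutive charts at 3 and 6 months". The food-based arm has the same rule, based on the daily food record chart: "The average intake will be calculated from a three non-consecutive records at 3 and 6 months". In both arms a resident is compliant at 75% or more and non-compliant below that. The definition speaks of the amount consumed daily, although the quantity calculated is an average.

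The researcher visits every month but determines compliance only at 3 and 6 months. Table 2 also ticks compliance at baseline, but randomisation followed baseline assessment, so that tick cannot supply data on the allocated intervention.

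**The concern.** Intake of a drink or snack varies from day to day, and a mean of three days carries much of that variation. When the mean is cut at 75%, residents whose usual intake lies near the cut-off can land on either side by chance. The sampled days also fall only around two time points. A resident lost before month 3 has no classification, and one lost between months 3 and 6 has only the first.

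The trial expects high mortality and attrition and sets its resident retention target at 65%, so losses could be sizeable. Compliance is one of the figures by which the interventions are judged acceptable, and components judged unacceptable are to be modified or removed in the definitive trial. At least in the ONS arm, the charts that would support a better measure are kept every day.

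**Working it through.** **1. The plan's own figures.** Two ONS give 2 × 300 = 600 kcal and 2 × 12 = 24 g protein. The cut-offs are 0.50 × 600 = 300 kcal and 0.75 × 600 = 450 kcal, as stated. Days used: 3 + 3 = 6 of about 180, or 3%.

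**2. Assumptions.** The documents give no mean or SD for the proportion taken. I assume a between-resident SD σb of 0.12 to 0.25 and a day-to-day SD σw of 0.10 to 0.30. Sampled days are taken as independent and representative.

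**3. Misclassification at 75%, by hand.** If usual intake and daily error are normal and half the residents truly reach 75%, the share misclassified on k days is arctan[σw / (σb√k)] / π.

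| σb | σw | k = 3 | k = 42 |
|---|---|---|---|
| 0.25 | 0.10 | arctan(0.231)/π = 7% | arctan(0.062)/π = 2% |
| 0.15 | 0.20 | arctan(0.770)/π = 21% | arctan(0.206)/π = 6% |
| 0.12 | 0.30 | arctan(1.443)/π = 31% | arctan(0.386)/π = 12% |

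Here 42 days means 7 per month for 6 months.

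**4. The same with intake bounded to 0–100%.** I simulated 200,000 residents per setting with beta-distributed usual intake (mean 70%, 75% or 80%; σb 0.12, 0.15 or 0.25) and beta-distributed daily intake (σw 0.10, 0.20 or 0.30). The daily variance was capped at 95% of its maximum for residents close to 0% or 100%. Misclassified at 75%: 5% to 32% on three days, 3% to 25% if all six days are pooled, and 1% to 12% on 42 days.

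**5. A coarse check for ONS.** Two servings on three days make six servings. If each is independently taken or refused, 75% needs at least 5 of 6. A resident who usually takes 80% passes with probability 6(0.8⁵)(0.2) + 0.8⁶ = 0.655 and so fails 34% of the time. One who usually takes 70% passes with probability 6(0.7⁵)(0.3) + 0.7⁶ = 0.42. Partial servings are recorded, so this overstates the noise.

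**6. Shift in the compliant share.** Under the normal model the observed share on three days is Φ(z·σb / √(σb² + σw²/3)), where Φ(z) is the true share.

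- True 60% (z = 0.253): σb 0.15, σw 0.20 gives Φ(0.253 × 0.15/0.189) = 58%. The worst case, 0.12 and 0.30, gives Φ(0.253 × 0.12/0.211) = 56%. The mildest, 0.25 and 0.10, gives 60%.
- True 70% (z = 0.524): 66% and 62% for the first two pairs.
- True 40%: by symmetry, 42% and 44% for the same two pairs, so the shift is upward.

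The bounded simulation agrees on direction. With mean 80%, σb 0.12 and σw 0.20 to 0.30, a true 70% reads as 60% to 64%. With mean 70% and the same SDs, a true 37% reads as 41% to 42%.

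**7. Sampling error for scale.** The plan expects 50 to 180 residents in three arms, so roughly 33 to 120 in the two dietetic arms. Around 60%, 1.96 × √(0.6 × 0.4/n) is ±17 points at n = 33 and ±9 at n = 120, ignoring clustering.

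**8. Average or daily.** In a bounded model, requiring every one of the three days to reach 75%, rather than their mean, turns a true 60% into about 35% to 50%.

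**9. Coverage.** Invented figures for illustration: if 65% of residents are classified at 6 months and 65% of them comply, while the 35% lost would have been 40% compliant, the figure for all residents is 0.65 × 0.65 + 0.35 × 0.40 = 56%. One figure passes 60% and the other fails.

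**The case against.** **Bias is not established.** A reader might infer that three-day sampling biases the criterion downward. That needs typical intake above 75% and a modest spread between residents, and the documents state neither. With typical intake at 70% and a small spread the shift is upward, and near a true 60%, where the decision lies, it is at most about 4 points. This part of the objection stands in full. Sampling error at these numbers is larger, and more chart days do not remove it.

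**The range depends on the assumptions.** This stands too. With a wide spread between residents, few lie near 75% and misclassification is low. A day-to-day SD of 30 points is impossible for a resident whose intake is close to 100%, so the upper end rests on the cap described in the working. If the two visits are pooled, six days rather than three apply.

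**Daily charting may not hold in both arms.** The drugs chart for ONS is explicitly daily. The food record chart is called daily, but it may be the same 24-hour chart of which Table 3 analyses three non-consecutive ones, and nothing states that it was kept throughout the 6 months. Chart completion is itself under test, with an 80% target. This limits the remedy and does not remove the point.

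**Losses may be handled elsewhere.** Descriptive statistics says that compliance collected throughout the trial will be summarised alongside withdrawals and deaths, and retention has its own criterion. That general sentence does not change the specific rule that compliance is determined at 3 and 6 months.

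**Compliance does not decide alone.** Crossover, staff adherence and the qualitative phase also bear on acceptability, and the analysis is descriptive. That lowers the stakes, but estimating compliance against these thresholds remains part of the trial's primary aim.

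**Conclusion.** The point holds as one of precision and coverage. Under the assumed SDs, three days misclassify about 5% to 32% of residents at 75%, against about 1% to 12% on 42 days. These figures concern the 75% cut-off only; I did not calculate them for 50%. Independently of any SD, residents who die or leave before 3 months contribute no compliance data.

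It does not follow that the criterion is biased. The compliant share can shift in either direction, by 10 points down or 5 points up at the extremes examined, and little near a true 60%. Losses could push the figure either way, depending on how residents who leave differ from those who stay. In a descriptive feasibility trial this is a moderate point, worth acting on because the change is cheap.

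**What to change.** - Calculate each resident's compliance as the mean proportion taken over all charted days, or over a pre-specified set of days spread across every month (for example 7 per month). Choose the days in the same way in both dietetic arms.
- Cover each resident's time in the trial, including residents who later die or withdraw.
- Apply the 50% and 75% criteria to that average and remove the wording about daily consumption. Report the mean percentage taken as well, since it does not depend on a cut-off.
- If food charts were not kept every day, use the same pre-specified days in both arms, so that the arms are measured alike.
- Keep the three 24-hour records for energy, protein and fluid intake.

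**Cost.** Extra abstraction of intervention entries from existing charts, with no new measurement and no dietary-software coding where the charts exist. Recruitment ended in December 2013 and phase 2 began in July 2014, so some of it would be retrospective, in a student project with limited resources. The result also depends on how complete the charts are, so the number of charted days per resident should be reported beside it.

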#### Standard care arm

The purpose of the standard care home first-line intervention is to provide an energy-dense diet [38], through the provision of small, frequent meals and/or recipe enrichment with additional calories, alongside prompting and assistance from care home staff where required. Standard care was provided within all six care homes, to ensure that no resident at risk of malnutrition was denied access to first-line treatment. Eligible residents within the two care homes allocated to standard care only received an energy-enriched diet, in line with the training already provided to care home staff (including catering teams), by the local nutrition support dietetic service. The care homes continued to receive monthly dietetic visits from the primary researcher, but individualised advice or plans were not provided.

### Safety considerations

#### Risk of re-feeding syndrome on initiation of an energy-fortified diet or ONS

Those at risk of re-feeding syndrome were identified through routine ‘MUST’ screening, if they had any of the following: a BMI of less than 16 kg/m [2], weight loss of greater than 15% over the last 3 to 6 months, no or negligible dietary intake for ten consecutive days [9]. If any resident was identified as being at risk of re-feeding syndrome at baseline, nutritional intervention was commenced cautiously, at 10 kcal/kg/day, increasing to provide the additional 600 kcal and 20–25 g protein by day 7. The dietitian also requested that the GP monitors electrolytes and glucose. This procedure is in line with usual, standard dietetic practice and national guidance [9].

#### Deteriorating swallow function (dysphagia) and an increased risk of aspiration

If dysphagia was identified or suspected during the 6-month intervention duration, by the care home staff or the primary researcher, this prompted a referral to the Speech and Language Therapy (SaLT) team, as per usual standard practice.

#### Decline of nutritional status in the standard care arm

If any resident in receipt of standard care without added intervention suffered a significant decline of nutritional status, dietetic intervention (food-based or ONS) was considered after 6 weeks of standard care, as per local and national best practice guidelines.

### Outcome measures

#### Primary outcome measures

Feasibility considerations:

Recruitment of care homes (ratio between those who consented to participate and those who were approached)The suitability of resident eligibility criteria (ratio between those who were considered eligible to enter the trial and those who were at risk of malnutrition)Residents’ willingness to participate in PROM’s (ratio between those who consented to participate and those who were eligible and approached)Resident retention in the trial (ratio between those who entered the trial and those that remained at 3 months and at 6 months)Data collection (ratio between completed questionnaires/screening tools/record charts and non-completed or unavailable questionnaires/screening tools/record charts) and physical outcome measurements (ratio between those residents measured and those that could not be measured)

Acceptability considerations:

Resident acceptability of allocated interventions (as measured by compliance and crossover rate in each intervention arm)Staff acceptability of allocated interventions (as measured by adherence to intervention plan)Resident acceptability of physical measurements (as measured by the ratio between those residents measured and those that refused)Resident acceptability of PROM’s data collection tools: appetite and dietary satisfaction VAS tool, EQ5D VAS and questionnaire, COOP quality of life tool. Questionnaire completion rates will be calculated

Secondary outcome measures:

Changes in nutritional status (malnutrition risk score, weight, body mass index, mid arm muscle circumference), functional status (hand grip strength), nutritional intake (energy, protein, fluid), healthcare resource usage and PROM’sUsefulness of resident completed questionnaires and tools (appetite and dietary satisfaction VAS, EQ5D VAS and questionnaire, COOP tool) and staff completed questionnaires and tools (sMMSE, healthcare resource usage). The ratio between those residents in the trial with capacity and those residents in the trial, but lacking capacity will be recorded. Questionnaire completion rates will be calculated and any third-party help used in completion will be recorded

### Descriptive variables

Following confirmation of resident eligibility, the staff in each care home completed a baseline assessment form for each resident. This form included the following information:Resident Trial Number (assigned by care home staff following screening)Resident genderCare home type (nursing, residential)Primary diagnosisDiagnosis of dysphagia (Yes or No). If Yes, to indicate recommended food and fluid modificationsDiagnosis of dementia (Yes or No)Risk of re-feeding syndrome (Yes or No). If yes, to indicate risk factor(s)Capacity (Yes or No)Informed consent received (Yes or NO)Height (to indicate whether measured, reported or an alternative measure)sMMSE score (for those with capacity only)

### Data collection and outcome assessments

#### Timing of assessments

Assessments were made at baseline, at 3 months and at 6 months (Table 2). All assessments were conducted within the care homes.

**Table 2 Tab2:** **Assessment schedule**

Measure	Completed by	Assessment time		
		Baseline	3 months	6 months
*Nutrient intake*	*Primary researcher*	✓	✓	✓
*Height*	*Care home staff*	✓	✓	✓
*Weight*	*Care home staff*	✓	✓	✓
*BMI*	*Care home staff*	✓	✓	✓
*Handgrip strength*	*Primary researcher*	✓	✓	✓
*MAC*	*Primary researcher*	✓	✓	✓
*TSF*	*Primary researcher*	✓	✓	✓
*sMMSE*	*Care home staff*	✓	✓	✓
*VAS*	*Participant rated*	✓	✓	✓
*EQ-5D*	*Participant rated*	✓	✓	✓
*CO-OP QoL*	*Participant rated*	✓	✓	✓
*Healthcare resource usage*	*Care home staff*	✓	✓	✓
*Compliance*	*Care home staff*	✓	✓	✓

*BMI* body mass index, *MAC* mid arm circumference, *TSF* tricep skinfold thickness, *sMMSE* Standardized Mini Mental State Examination, *VAS* visual analogue scale, *EQ-5D* Euroqol 5 dimensions, *QoL* quality of life.

#### Outcome measurements

One objective of this trial is to evaluate the feasibility and acceptability of a range of quantitative outcome tools and assessment methods for use within a definitive trial (Table 3). The assessments to be evaluated included change in energy and protein intake, anthropometric parameters (weight, BMI, handgrip strength, MAMC) and patient-centric measures such as health state (EQ-5D), quality of life (CO-OP), participant-rated appetite and dietary satisfaction (VAS).

**Table 3 Tab3:** **Quantitative outcome assessments**

Outcome	Completed by	Assessment
*Handgrip strength (kg)*: an index of general upper extremity strength (function)	*Primary researcher*	Measured using a handgrip dynamometer on the non-dominant arm [39].
		Limitations include the influence of debility, age and familiarity with the technique. The number of residents that refuse to participate, or for whom the measurement is not feasible, will be recorded.
*Mid arm muscle circumference (MAMC) (cm)*: an estimate of muscle mass	*Primary researcher*	Calculated using mid-upper arm circumference (MUAC) (measured with a tape measure) and tricep skinfold thickness (TSF) (measured with a standardised skinfold calliper): *MAMC (cm) = MUAC (cm) − 3.14 × TSF (cm)*
*Mean energy (kcal), protein (g) and fluid intake (ml):*	*Primary researcher*	Calculated from analysis of three non-consecutive 24-h food record charts. Usual tableware such as bowls, plates and glasses will be measured in each care home at baseline, and the size/capacity will be recorded.
		Nutrient intake will be determined using the dietary analysis software package *Diet Plan 6* (Forestfield Software Ltd, West Sussex, UK), which is installed with the complete set of UK food tables.
*Height (m)*	*Care staff measured*	Taken from clinical records or measured using a stadiometer. If standing height cannot be measured, self-reported height is considered the superior secondary method, or ulna length can be measured to obtain an estimate. Information on the method used to measure height will be collected.
*Weight (kg)*	*Care staff measured*	Measured using clinical calibrated standing, chair or hoist scales. Information on the method used to measure weight will be collected.
*Body mass index (BMI) (kg/m* ^*2*^ *)* A measure of adiposity	*Care staff measured*	Calculated using: *weight (kg)/height (m* ^*2*^ *).*
		Validity is limited by the influence of gender, ethnicity and age on body composition, which is not accounted for within the calculation [40]. Reliability is also questionable in the presence of confounding factors including oedema or ascites [41].
*Healthcare resource usage*	*Care staff measured*	The healthcare resource usage questionnaire to be piloted within this trial has been developed from consideration of existing instruments submitted for use in residential care settings on the ‘MRC Database of Instruments for Resource Use Measurement’ (DIRUM). The questionnaire will be completed by care home staff, from baseline to 3 months and from 3 to 6 months for each participating resident.
*Health state using The EuroQol-5D (EQ-5D)*	*Participant rated*	There is no malnutrition-specific measure of health state or quality of life for patients, so these well-established and validated measures will be piloted within this population to inform as to whether they are appropriate for completion by care home residents with varying cognitive function. The Euroqol group and the Dartmouth CO-OP project have granted permission to use the tools
*Quality of life using the CO-OP Quality of life chart*	*Participant rated*	
*Visual analogue scale (VAS) for self-perceived appetite and dietary satisfaction*	*Participant rated*	A VAS tool has been developed to measure the following subjective sensations; ‘hunger’, ‘appetite’, ‘dietary satisfaction’, ‘pleasantness of meals’, ‘pleasantness of snacks’ and ‘pleasantness of drinks’ and will be piloted within this trial.

